# Effectiveness of 38% Silver Diamine Fluoride Application along with Atraumatic Restorative Treatment for Arresting Caries in Permanent Teeth When Compared to Atraumatic Restorative Treatment in Adults—Study Protocol for a Randomized Controlled Trial

**DOI:** 10.3390/mps5060087

**Published:** 2022-10-26

**Keywords:** atraumatic restorative treatment, caries arrest, dental caries, silver diamine fluoride, survival of the restoration

## Abstract

Introduction: Dental caries in the adult population that require preventive and therapeutic treatment are generally neglected in rural communities. The determination of the effectiveness of the application of 38% silver diamine fluoride (SDF) in arresting caries lesions when combined with atraumatic restorative treatment (ART) is very important, as it serves as a preventive and restorative procedure to regain the function of the permanent dentition. The assessment of optimal SDF application with ART, in comparison with ART alone, in managing cavitated carious lesions in a pragmatic setting, is the need of the hour to recommend optimal dental care, especially in rural settings which have minimal access to comprehensive dental care. Methods and Analysis: The clinical trial will enrol 220 adults (18–65 years) with cavitated carious lesions attending the Amrita School of Dentistry in the Ernakulam district, India. This study is a randomized, controlled trial with a 1:1 allocation ratio in two parallel groups. Study arm 1 will receive 38% SDF application and ART, and study arm 2 will receive ART only. A digital radiograph will be taken immediately after restoration (baseline) as well as at the end of the 6th month for evaluation of caries arrest. The assessment of the survival of the restoration will be done on the 7th day, 30th day, and at the end of the 6th month. The final analysis would include both the tooth and person levels. Ethics and Dissemination: This trial adheres to the principles of the Declaration of Helsinki and the guidelines of the Indian Council of Medical Research (ICMR). This study protocol has been approved by the Institutional Review Board. This trial has been registered prospectively with the Clinical Trial Registry of India (Registration No: CTRI/2021/12/038816).

## 1. Introduction

Oral health is essential to overall health and well-being. The global prevalence of oral diseases is estimated to be almost 3.5 million people worldwide. The lack of availability, accessibility, and affordability of basic oral health care is a significant problem in low- and middle-income countries, particularly amongst rural populations [1]. The sequelae of typical untreated oral diseases are commonly excruciating. They can constitute unrelieved discomfort, debilitated quality of life, and shortened work efficacy. Oral diseases impose a high financial crisis on families and the medical system due to treatment costs incurred [2]. Since the early appearance of dental caries is mostly asymptomatic, most of the population refrains from seeking oral care, which can lead to painful events in the future.

According to the World Health Organization, the population of people above the age of 65 years is increasing at a rate of 2.5% annually. This shift in the age distribution of the population will be markedly experienced in developed, as well as lesser-developed countries, by 2050. Poor oral health is deleterious to the holistic state of well-being [3]. Dental caries is the least treated disease among older adults. The prevalence of dental caries is found to be 50–84% among the adult population of India [4,5]. Early treatment of dental caries with the advent of new techniques and novel materials enables minimally invasive and less expensive treatment today. Preventive interventions are the most effective treatment against dental caries. The most frequently used preventive interventions are the application of pit and fissure sealants and fluoride varnish [6]. Currently, the state of the art of caries treatment is represented by resin-based composite restorations either in anterior or posterior teeth [7,8,9].

Atraumatic restorative treatment (ART) is a highly successful community-based approach for the treatment or secondary level of prevention of dental caries. It is an alternative approach for managing dental caries which involves the removal of infected tooth tissue using conventional hand instruments alone, without the use of anesthesia and rotary equipment. One of the indications for the pertinent use of ART concerned the elderly, particularly those who are impaired. The first such study on atraumatic restorative treatment was carried out amongst elderly subjects who were housebound due to psychiatric, physical, or psychological problems. After 1 year of placement, 79% of the ART restorations were considered successful [10]. In a two-year randomized controlled trial, ART presented the probability of survival rates of 84% compared to conventional techniques, consisting of the preparation of (the decayed) tooth using a rotary instrument (for removal of infected tissues) under local anesthesia, followed by resin-modified glass ionomer cement restoration [11]. When the effect of ART on adult patients’ comfort was assessed, it was noted that ART caused less anxiety than the traditional restorative methods using rotary instruments as the vibration and sound of the rotary instruments were absent [12].

ART is an important component of the Basic Package of Oral Care (BPOC) which also includes Affordable Fluoride Toothpaste (AFT), and Oral Urgent Treatment (OUT). This has been recommended by the WHO, and has been a successful community-based approach to reducing the burden of dental caries [13]_._ Considering the global rise of the elderly population with natural dentition in the coming decennium, a study covering the effectiveness of the ART approach, as part of a package of oral care for use among the adult population, should receive serious attention. However, the ART approach is not successful in some cases, especially in cavities that are less accessible through conventional hand instruments. Improper removal of caries lesions may lead to bacterial invasion, secondary caries, and failure of restoration [14].

Advanced dental caries preventive technology comprises treatment with various remineralizing agents. Silver diamine fluoride (SDF), introduced in 1969, has been used for the management of dentin hypersensitivity and to arrest dental caries. The Central Pharmaceutical Council of Japan’s Ministry of Health and Welfare accepts a 38% SDF solution as a dental treatment for caries [15]. SDF (38% *w*/*v* Ag (NH_3_)2F, 30% *w*/*w*) is a colourless topical agent. It is composed of 24.4–28.8% (*w*/*v*) silver, 5.0-5.9% fluoride, and ammonia at pH 10 [16]. A layer of the silver-protein conjugate is formed when silver diamine fluoride is topically applied to a decayed tooth. This enhances resistance to acid effect and digestion by enzymes. Silver diamine fluoride outperforms other anticaries medicaments as the silver and fluoride ions permeate 25 microns into the enamel and about 50–200 microns into dentinal tubules. The fluoride ions advance remineralization, and silver ions have effective antimicrobial action. The application of SDF is simple, painless, and non-invasive [17].

Remarkable results were noted in elderly patients when SDF was applied annually for the prevention and arrest of occlusal surface caries as well as root caries [18]. Rosenblatt et al. recommend SDF application as a more effective caries preventive intervention than fluoride varnish and observe it to be an effective, efficient, safe, and affordable caries-preventive agent that meets the WHO Millennium Goals criteria for 21st-century medical care [19]. Application of 38% SDF solution is recommended over the use of 5% sodium fluoride varnish to better arrest cavitated carious lesions on the coronal tooth surface of permanent dentition [20]. The current clinical trial reports on SDF application support its effectiveness in preventing and cessation of radicular caries, deep coronal lesions remineralization, along with hypersensitive dentin treatment [21,22].

However, one of the noted drawbacks of SDF application is its potential to cause discoloration of the teeth and oral tissues [17]. Black staining is an often-reported side effect of SDF application and influences the acceptability of this therapy. The use of potassium iodide (KI) directly after SDF application results in masking the staining of the affected dentine [23]. Applying KI over SDF creates an insoluble layer of yellow precipitate of silver iodide, thus obscuring the black staining on the tooth [24]. The effectiveness of SDF in preventing caries progression was not affected by the application of KI [25]. The application of saturated potassium iodide solution to reduce discoloration was not found to be effective in altering or preventing caries in a study among community-dwelling senior citizens [26].

Due to their safety, efficiency, feasibility, and effectiveness in dental caries management, ART and SDF are employed in routine treatments for all age groups. Yet if the initial prevention strategies fail, there is a need for effective management to arrest the disease, restore the cavitated tooth, and reduce the negative impact of caries lesions. The silver modified atraumatic restorative technique, known as the SMART technique, is a modification of ART, as stated in a case report, wherein the application of SDF is followed by conditioning with polyacrylic acid and restoration of the cavitated tooth with GIC [27]. By using SMART with chemically sealed restoration, the nutrient source for any persistent bacteria is cut off, thus killing the microbes, arresting and remineralizing the caries dentin, preserving the remaining tooth structure, and enhancing the pulp vitality [27]. The application of an antimicrobial agent like SDF before the placement of a restoration proved to be more effective, slowing the progression of the carious lesion [28]. There are no reports which suggest hampering of shear bond strength of glass ionomer cement to carious dentine by the application of KI solution after SDF placement [29,30].

According to the socioeconomic census in India in 2011, 68% of the population is still living in rural areas [31] where the possibility of health systems integrating to their fullest extent is still a difficult task. Therefore, easily accessible and less expensive treatments should be promoted for changing the population’s attitude towards dentistry, although India has been advancing in various aspects of oral health [32]. Educating on new concepts that can be easily perceived and applicable through community health workers and dental auxiliaries in society can bring about a drastic change in this prejudice about dental well-being. With the advancement of community-based procedures such as atraumatic restorative treatment and silver diamine fluoride application more attention can be bought to the population towards dental care and its importance.

A combination of SDF application and ART together would be an innovative, minimally invasive method that imparts both bactericidal effects leading to caries arrest and restores the function of the tooth. Thus, we would be able to better address the drawbacks of both these procedures when applied individually. Such a combination of 38% silver diamine fluoride application along with atraumatic restorative treatment on the cavitated carious lesion of permanent teeth in adults has not been reported in the literature. If found successful, this would be an extremely valuable technique that will be of great advantage for oral health in community-based projects.

The objective of the clinical trial is to compare the effect of the application of 38% SDF along with atraumatic restorative treatment, against atraumatic restorative treatment alone, in arresting active occlusal carious lesions on permanent teeth. It also intends to compare the survival of the restoration. The trial also assesses the patient satisfaction and acceptability of the application of the SDF.

## 2. Methods

### 2.1. Study Design

This is a randomized, controlled trial with two parallel comparator arms, having a 1:1 allocation ratio (Figure 1).

### 2.2. Study Settings

The trial will be conducted at Amrita School of Dentistry, Amrita Institute of Medical Sciences, Kochi, India.

### 2.3. Trial Registration

The trial protocol has been registered with the Clinical Trial Registry of India at http://ctri.nic.in accessed on 1 November 2021. (Registration No: CTRI/2021/12/038816 dated 21 December 2021, Registered on 2 November 2021). Recruitment of study participants will begin in August 2022 and the trial is anticipated to conclude by December 2024. This clinical trial protocol has been developed following the SPIRIT 2013 Statement (https://www.spirit-statement.org/ accessed on 10 August 2020).

### 2.4. Study Population

Any individual between 18 to 65 years with one or more cavitated carious lesions in the occlusal and/or proximal surface of the permanent posterior teeth.

### 2.5. Eligibility Criteria

#### 2.5.1. Inclusion Criteria

Male or female individuals, between the age of 18 to 65 years, with either one of the following: Class 1 caries (only occlusal surface involved in posterior teeth) or Class 2 caries (occlusal and proximal surface of posterior teeth), without involving the pulp.Patients understand the significance of SDF and ART for the treatment and prevention of tooth decay.Patients are willing to attend the follow-up visits as required for the trial.Patients will be enrolled irrespective of special needs if they are willing and able to comply with all the trial requirements.Patients with the absence of periodontal disease.

#### 2.5.2. Exclusion Criteria

Patient with stomatitis or ulcerative gingivitis.Developmental abnormalities of enamel and dentin.Serious non-communicable medical conditions include cardiac failure and poor glycaemic control.Cavitated teeth missing greater than a third of the coronal tooth structure or having pulpal involvement. Pulp-exposed tooth, obvious discoloration, premature hypermobility, or presence of a periapical abscess or a sinus will be regarded as a tooth with pulpal involvement.Known silver allergy.During the intervention, if there is inadvertent pulp exposure, the patient will be excluded from the study.

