### 2.7. Interventions

After patient selection, the treatment will be given to the patient according to the selection process. The study participants will be allocated to either one of two parallel arms.

Study arm 1: will receive SDF application and ART restoration.

Study arm 2: will receive ART restoration.

All treatment will be done in a dental chair.

At the baseline visit, an assessment of cavitated caries lesions will be done on all the study participants. The ADA Caries Risk Assessment Form (Age > 6) would be used to assess the risk. Depending on the study arm, ART with or without SDF will be applied to selected teeth (Figure 1). The demographic features of participants and their caries status will be recorded.

*Procedure to be followed for study arm 1:*

A preoperative photograph of the selected tooth will be taken. The caries lesion entrance will be widened and with help of a dental hatchet, the thin unsupported frangible enamel will be removed. In the next step, the decayed tissue will be excavated with a spoon excavator, first at the dentin enamel junction and thereafter from cavity walls and the pulpal floor. The cavity will then be rinsed with water and air-dried, followed by isolation with cotton rolls.

*Application of Silver Diamine Fluoride*

Using a disposable micro applicator tip, the SDF (e-SDF, 38% silver diamine fluoride, Kids-e-dental LLP, Globus Medisys, Mumbai, India) will be applied to the walls of the prepared cavity for 10 s and allowed to air dry for one minute. One drop of 38% SDF solution (2.24 F-ion mg/dose) would be required per tooth. A saturated solution of potassium iodide (Lugol’s Iodine solution 5%, Bio balance, Pali Marwar, Rajasthan, India) will be applied with a different microsponge to decrease color change and will be repeated 1-3 times until no further black discoloration is observed [17].

*Placement of ART restoration*

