### 2.14. Adverse Events

38% SDF solution and glass ionomer cement, employed in regular dental practice for standard dental procedures, are the agents used for this trial. There are minimal potential risks for the study participants, such as the risk for the patients receiving oral care in a routine clinical setting. The most expected adverse effect is an allergic reaction to SDF. All grades of adverse events occurring to the participants during the treatment and follow-up period will be recorded and reported. The principal investigator would obtain information about adverse events with the help of standard questions and an oral examination at every planned visit of the study participant.

The participants may experience an unpleasant metallic taste. Silver diamine fluoride can cause a “transient pigmentation” of the skin, buccal mucosa, or tooth surface. This is not harmful and resolves itself with exfoliation of skin and mucosa within 2 weeks. Universal precautions would be taken to prevent exposures. A cotton roll isolation of the concerned tooth and application of cocoa butter would be carried out to protect surrounding oral tissues from accidental exposure to SDF.

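### Minor, patient safety only: silver is the only allergy exclusion and section 2.14 does not name the iodide solution, so a patient with known iodine or iodide hypersensitivity is eligible as printed

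*Protocol article*

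**What the plan says.** - **Section 2.5.2 (Exclusion Criteria)** has one allergy item: "Known silver allergy". The other items cover oral disease, developmental defects of enamel and dentin, serious medical conditions (cardiac failure and poor glycaemic control are named), extensive or pulpal tooth damage, and accidental pulp exposure during treatment. None covers iodine or iodide.
- **Section 2.5.1 (Inclusion Criteria)** has no allergy item. Its understanding criterion names two components: "Patients understand the significance of SDF and ART for the treatment and prevention of tooth decay".
- **Section 2.7 (Interventions)**, in the arm 1 procedure after SDF, specifies "A saturated solution of potassium iodide" (product given as Lugol's iodine 5%), which "will be applied with a different microsponge to decrease color change". The step is repeated one to three times and is not described as optional. Arm 2 does not receive it.
- **Section 2.14 (Adverse Events)** opens: "38% SDF solution and glass ionomer cement, employed in regular dental practice for standard dental procedures, are the agents used for this trial". It continues "There are minimal potential risks for the study participants" and then "The most expected adverse effect is an allergic reaction to SDF". Iodide and iodine do not appear in the section. The section does provide for recording adverse events of every grade, with standard questions and an oral examination at each planned visit.

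**The concern.** The protocol accepts that a known allergy to the silver agent is a reason not to enrol. It does not extend that protection to the iodide, which is the next solution applied to the same cavity. A screener who follows the printed criteria exactly would admit a patient with a known iodine or iodide hypersensitivity. If that patient were allocated to arm 1, the operator would either apply the iodide or depart from the arm 1 procedure after randomization. Arm 2 has no equivalent problem.

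What is at stake is an avoidable exposure for an individual patient. Recording adverse events (section 2.14) and following patients who withdraw because of one (section 2.12) capture a reaction after it has happened. They do not prevent the exposure.

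**Working it through.** The plan has no figure to reproduce. The check is a comparison of sections, followed by simple scaling to judge the order of size.

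**1. Agents applied, against the safety text**

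| Material | Where applied | Allergy exclusion in 2.5.2 | Named as a trial agent in 2.14 |
|---|---|---|---|
| SDF (silver) | Arm 1 | Yes | Yes |
| Potassium iodide / Lugol's iodine | Arm 1 | No | No |
| Glass ionomer cement | Both arms | No | Yes |
| Polyacrylic acid conditioner | Printed for arm 2 | No | No |
| Petroleum jelly | Both arms | No | No |

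The iodide is a routine arm 1 solution that is missing from both safety sections. The table also shows that it is not the only material missing from them; this is taken up under the objection.

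**2. Following one patient through the printed steps**

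Take a patient with a known iodine hypersensitivity who is otherwise suitable. No item in 2.5.1 or 2.5.2 removes this patient. Section 2.12 then randomizes 1:1. If the result is arm 1, section 2.7 applies the iodide.

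**3. Scaling**

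- Inputs from the article: 110 patients per arm and 220 in total (section 2.11); screening continues until 220 are reached (section 2.12).
- Assumed input, not in the documents: the share p of otherwise eligible patients with a known iodine or iodide sensitivity, shown for 0.1% to 1%.
- Expected number in arm 1 = 110 × p, which is 110 × 0.001 = 0.11 to 110 × 0.01 = 1.1.
- Extra patients to screen if they are excluded = 220/(1 − p) − 220, which is 220/0.999 − 220 = 0.22 to 220/0.99 − 220 = 2.22.

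The first result counts patients with a known sensitivity who would be allocated to arm 1. It does not count reactions. Both results move in proportion to an assumed p, so they show only that the numbers on either side are small.

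**The case against.** **This is a condensed article.** Full contraindication lists and allergy questions are often left to the full protocol and the record forms, and those may cover iodide. That limits the point to the text as printed. It does not remove it: the article prints itemized eligibility criteria that include an allergy item, and that item covers one of the two solutions applied in sequence in arm 1.

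**The exclusion may be meant only for the investigational agent.** There is no allergy exclusion for glass ionomer, polyacrylic acid or petroleum jelly either, and no section states a hazard for iodide; the Introduction discusses it only for staining, caries effect and bond strength. This is fair, and it keeps the point at the lowest grade. What remains is that the iodide is a routine step specific to arm 1 and, unlike glass ionomer, is not mentioned in the risk section at all.

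**Stronger readings that a reader might infer, and that the documents do not support:**

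- *Section 2.14 contradicts section 2.7.* Section 2.14 does not say that its two agents are the only ones, and it also leaves out ancillary materials. It is an incomplete risk statement, not a contradiction.
- *Nothing in recruitment would prompt a patient to mention an iodine sensitivity.* Sections 2.5.1 and 2.12 name only SDF and atraumatic restorative treatment. However, section 7 provides a printed information sheet and time for discussion, and the sheet is not shown. Routine history-taking might also find the allergy, although the article does not say so.
- *There is a 10% to 67% chance of a problem.* Under the same assumed p, 1 − (1 − p)^110 gives 10.4% at 0.1% and 66.9% at 1%. That is the chance of at least one such patient in arm 1 if nobody acts on the known sensitivity. It is not a chance of harm, and it rests wholly on an assumed prevalence. It should not be quoted as the size of the point.

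**Conclusion.** The point holds as a minor patient-safety matter. As printed, a patient with known iodine or iodide hypersensitivity is eligible and would be exposed to the iodide if allocated to arm 1, and the risk statement in section 2.14 does not take that agent into account.

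The size is unknown and probably very small. The documents give no prevalence of sensitivity and no hazard for a small local application, and the true number of affected patients may be zero. Power, type I error and the comparison of caries arrest and restoration survival are not affected. The conclusion rests on the printed criteria being the ones applied; if the full protocol or the screening form already asks about iodine, only the wording of the article needs correcting.

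**What to change.** 1. In section 2.5.2, replace the silver item with: *Known allergy or hypersensitivity to silver or to the iodine/iodide solution.*
2. Ask this of all patients at eligibility screening, before the allocation code is revealed. Section 2.12 already withholds the code until baseline assessments are complete, so the exclusion falls on both arms alike and cannot unbalance them.
3. In section 2.14, add a sentence that names the iodide solution as an arm 1 agent.

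**Cost.** One screening question and very few extra patients screened. The target of 220 is kept, because screening continues until it is reached. Recruitment was planned to begin in August 2022 (section 2.3) and the article was published on 26 October 2022. If enrolment had started, the change also needs a minor amendment to the ethics-approved protocol.
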